## 3. Analyses of Results

All continuous variables will be presented as the mean (±SD) or the median (IQR) with categorical variables presented as frequencies or percentages. For the efficacy component of the study, paired *t*-tests will be used to identify whether outcome measures change over time. After adjusting for potential covariates, analysis of covariance (ANCOVA) will be applied to identify differences between diet groups over time, with the dietary groups as the independent variable and outcome parameters (primary and secondary outcomes) as the dependent variable. All quantitative analyses will be performed using Statistical Package for the Social Sciences (SPSS) for Windows 26.0 software (IBM Corp., Armonk, NY, USA), with statistical significance set at *p* ≤ 0.05. Primary analyses will be carried out with results analysed based on the “intention to treat” protocol. The required sample size for the proposed study is powered based on change in HOMA-IR (primary outcome of the study) as reported by Ryan et al. [71]. For the proposed study, it was estimated that a total of *n*  =  32 participants would provide 80% power to detect a significant (*p*  <  0.05, 2-sided) change in HOMA-IR by 1.7 ± 0.5. Assuming an attrition rate of 30%, the target sample size for the proposed study will be *n*  =  42 participants (MedDiet intervention *n* = 21; HE dietary approach *n* = 21).

For the acceptability and feasibility component of the study, all semi-structured interviews will be audio-recorded and transcribed verbatim. Data will be analysed through open coding, whereby codes will be iteratively revised and deductively clustered into subthemes and themes according to the framework technique proposed by Richie et al. [72]. These themes will then be mapped against the COM-B constructs. All participant interviews, coding and theme development will be performed by NS. To ensure reliability, successive 10% of the transcripts will be independently coded by another member of the research team until consistent coding occurs. In the event of discrepancies, coded transcripts will be discussed and recoded until a consensus is reached. Analyses of qualitative data will be performed using NVIVO software (QSR International, Melbourne, Australia), version 12.

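### Read as mean ± SD, a HOMA-IR change of 1.7 ± 0.5 does not give n = 32, so the 80% power is not tied to any stated difference between the diets

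*Protocol article*

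**What the plan says.** All of the relevant text is in the protocol article, section 3 (Analyses of Results).

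- The study is "powered based on change in HOMA-IR (primary outcome of the study"), with the effect taken from a cited study.
- A total of 32 "participants would provide 80% power to detect a significant" result at two-sided p < 0.05, where the effect is given as a "change in HOMA-IR by 1.7 ± 0.5".
- The target is then raised: "Assuming an attrition rate of 30"%, 42 are to be randomised, split as "MedDiet intervention *n* = 21; HE dietary approach *n* = 21".
- Two efficacy analyses are planned: paired t-tests for change over time, and an ANCOVA "to identify differences between diet groups over time".
- The only other use of ± in the article is in the same section: "All continuous variables will be presented as the mean (±SD) or the median (IQR").

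The sizing sentence does not name the test used, does not label the ±, and does not say whether 1.7 belongs to one arm or to the contrast between arms.

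**The concern.** The sentence supplies an effect, a spread, an alpha, a sidedness, a power and a sample size. Under the article's own convention for ± these do not agree with one another, and the gap is far too wide for rounding or choice of formula to explain.

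The contrast is also unclear. The comparator is active: section 2.9 gives the healthy-eating (HE) arm a prescribed, individualised diet, and sections 2.10 and 2.11 give both arms the same counselling schedule, information pack and weekly texts. A change seen within one arm therefore need not equal the MedDiet–HE difference that the ANCOVA estimates.

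This sentence is the only justification given for enrolling 42 women. If the detectable between-diet difference is not known, a reader of a null result cannot tell what size of benefit the trial was able to find.

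**Working it through.** **Inputs (section 3).** Effect 1.7; spread 0.5 (unlabelled); two-sided alpha 0.05; power 80%; evaluable n = 32, so 16 per arm at 1:1; 42 randomised; attrition 30%. No baseline correlation is given, so the calculations use unadjusted t-tests.

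**Method.** Two-sample power = P(T > t₀.₉₇₅,df), where T is noncentral t with df = n₁ + n₂ − 2 and noncentrality d/√(1/n₁ + 1/n₂). For a paired test, df = n − 1 and noncentrality d√n.

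**Step 1: try to reproduce n = 32 with 0.5 as an SD.** d = 1.7/0.5 = 3.4.

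- Normal approximation: n per arm = 2 × [(1.960 + 0.842)/3.4]² = 1.36, so 2 per arm.
- Two-sample t: power 0.459 at 2 per arm and 0.869 at 3 per arm (noncentrality 3.4 × √1.5 = 4.16, df 4). So 3 per arm, 6 in total.
- Paired t: power 0.825 at n = 3.
- At the plan's 16 per arm: noncentrality 3.4 × √8 = 9.62, power above 99.99%.

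The stated figure is not reproduced.

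**Step 2: what n = 32 requires.** At 16 per arm, 80% power needs d = 1.024 (0.991 by the normal approximation). This means either:

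- an SD of 1.7/1.024 = 1.66 for a difference of 1.7 units, or
- a difference of 1.024 × 0.5 = 0.51 units for an SD of 0.5.

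A paired test on all 32 needs d = 0.511, so an SD of 1.7/0.511 = 3.33 for a change of 1.7. The article states none of these.

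**Step 3: other readings of 1.7 ± 0.5.**

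| Reading | Total n for 80% power |
|---|---|
| 0.5 is the SD at each time point, uncorrelated (SD of change 0.5√2 = 0.71) | 6 (normal) to 8 (t) |
| Roles swapped: difference 0.5, SD 1.7 | 364 to 366 for two arms; power at 16 per arm about 13% |
| 0.5 is a 95% CI half-width, source n of 12, 16 or 32 (assumed) | 12, 14 or 26 |
| 0.5 is a standard error, source n of 10 (assumed) | 28 to 30 |
| 0.5 is a standard error, source n of 11 (assumed) | 30 to 32 |
| 0.5 is a standard error, source n of 12 (assumed) | 34 to 36 |

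Of these readings, only the standard-error one lands on 32. It does so at a source size of (1.66/0.5)² = 11.0, which is back-solved from 32 and appears nowhere in the article.

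**Step 4: detectable difference under the plan's own attrition.** 42 × 0.70 = 29.4 completers, or 14.7 per arm. There, 80% power needs d = 1.07, and power for 1.02 SD is about 76%. With 16 completers per arm the figure is 1.02.

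**The case against.** **The fault may be only a missing label.** If 0.5 is a standard error from about 11 participants, 32 comes out. The ± convention rests on a single other instance, which governs how the trial's own results will be presented and does not label an input from another study. This stands in part: it would be wrong to say that the original calculation is known to be mistaken. But the source size is back-solved, and a sentence that works only with an unstated label and an unstated source size does not support its own figure as written.

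**The word change may simply name the outcome variable.** The abstract defines the primary outcomes as changes, so 1.7 could be a between-diet difference in change. A reader might infer that 1.7 is a within-arm figure misapplied to a between-arm test. The text does not support that; it is ambiguous, and the point is only that it must be settled.

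**A reader might infer that the trial is underpowered.** The documents do not show this. Taken literally, 1.7 ± 0.5 makes 32 far more than enough. Even if HE achieved half of the 1.7 (an assumption), d = 0.85/0.5 = 1.7 and power at 16 per arm is 99.6%. Low power appears only on adding two assumptions: an SD of 1.66, itself derived by taking n = 32 as right, and an HE response of 25% or 50% of 1.7. Power would then be 56% or 29%, but these figures are purely illustrative.

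**ANCOVA.** Baseline adjustment may improve precision by an unknown amount. It would lower the required n, so it cannot explain a rise from 6 to 32.

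**Scale of the study.** Section 4 calls it small and its evidence preliminary. This reduces, without removing, the risk that a null result is misread.

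**Conclusion.** The inconsistency holds. With ± read as SD, the stated inputs need about 6 participants for a two-arm comparison or 3 for a paired test, against the stated 32, and 16 per arm would give more than 99.99% power where the article claims 80%. To obtain 32 for a two-arm difference of 1.7, the SD must be about 1.66, which the article does not give. Because the contrast is unstated as well, the 80% power cannot be attached to any particular MedDiet–HE difference.

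The conclusion stops there. It does not establish that the trial is too small, that the source was misread, or that 1.7 is a within-arm change. The calculations assume 1:1 allocation, unadjusted t-tests and two-sided 0.05.

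**What to change.** Keep 42 randomised. Go back to the cited study and state (a) whether 0.5 is an SD or a standard error, giving the SD of change, and (b) whether 1.7 is a within-arm change or a between-diet difference. Then replace the sizing sentence with one expressed as the contrast the ANCOVA tests, for example:

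> With 42 randomised and 30% attrition (about 29 completers, 14–15 per arm) and two-sided alpha 0.05, the trial has 80% power for a between-diet difference of about 1.07 SD in HOMA-IR change (1.02 SD if 16 per arm complete), before any gain from baseline adjustment.

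Once the SD is confirmed, add the same difference in HOMA-IR units and say why a difference of that size between the two diets is plausible.

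The cost is a check of one source and one rewritten sentence, with no extra participants and no change to design or analysis. The downside is that the stated detectable effect becomes less favourable.

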## Abstract

Polycystic ovary syndrome (PCOS) is a common endocrine condition in reproductive-aged women associated with metabolic, reproductive and psychological features. Lifestyle modification (diet/physical activity) is considered first-line treatment for PCOS. However, there is limited high-quality evidence to support therapeutic dietary interventions for PCOS beyond general population-based healthy eating guidelines. Adherence to a Mediterranean diet (MedDiet), with or without energy restriction, improves cardiometabolic health in populations including persons with or at high risk of cardiovascular disease and type 2 diabetes. However, there is limited research examining the MedDiet in PCOS. Therefore, this 12 week randomized controlled trial will investigate the efficacy of a MedDiet on cardiometabolic and hormonal parameters and explore its acceptability and feasibility in PCOS. Forty-two overweight and obese women with PCOS (aged 18–45 years) will be randomized to receive dietary advice consistent with Australian Dietary Guidelines or an ad libitum MedDiet intervention. All participants will receive fortnightly counselling to facilitate behaviour change. The primary outcomes will be changes in insulin resistance, glucose, total testosterone and sex hormone-binding globulin. Secondary outcomes include changes in body weight and feasibility and acceptability of the MedDiet intervention. The results of this study will provide further evidence on specific dietary approaches for management of PCOS.

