In a secondary analysis of four clinical trials assessing the effect of weight loss on anthropometric, reproductive, metabolic and/or psychological outcomes in women with PCOS (*n* = 221), Moran et al. [73] reported that although 63% of women achieved clinically significant weight loss of ≥5% over a 2–8 month intervention period, up to 47% of women were lost to attrition, which is also consistent with previous literature [74,75,76]. Given that IR is a prominent clinical feature in the pathophysiology of PCOS, a dietary approach based on key principles of a MedDiet, without the need for weight loss, may indeed represent a novel dietary intervention for women with and without obesity. In a case–control observational study of Italian women (*n* = 112 with PCOS; *n* = 112 controls), greater adherence to a MedDiet was inversely associated with IR and hyperandrogenemia [77]. Moreover, the investigators further reported marked differences in the habitual dietary behaviours between the two groups, whereby women with PCOS consumed less EVOO, legumes, fish/seafood, and nuts compared to women without PCOS. In corroboration with the aforementioned study, Cutillas-Tolín et al. [78] reported that adherence to a MedDiet was protective against clinical phenotypic features of PCOS, namely hyperandrogenism and oligo-anovulation. Moreover. Barrea et al. [79] recently reported that poor adherence to a MedDiet was associated with a ‘metabolically unhealthy obesity’ phenotype in women with PCOS, as defined through evaluation of endocrine-metabolic profiles, inflammatory status, cardiometabolic indices and body composition parameters. Nevertheless, the absence of well-designed clinical trials exploring the efficacy of a MedDiet intervention in women with PCOS represents a notable gap in the research literature.

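### Randomising 42 with 30% attrition leaves about 29 completers, short of the 32 on which the stated 80% power rests

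*Protocol article*

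**What the plan says.** Section 3 of the protocol article gives the sample size in two steps. The first sets the number needed for analysis: "32 participants would provide 80% power to detect a significant" difference at two-sided 0.05, described as a "change in HOMA-IR by 1.7 ± 0.5". The second adds an allowance for dropout: "Assuming an attrition rate of 30%, the target sample size for the proposed study will be" 42, divided as "MedDiet intervention *n* = 21; HE dietary approach *n* = 21". The Abstract gives the same total as the number to be randomised: "Forty-two overweight and obese women with PCOS (aged 18–45 years) will be randomized".

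The allowance formula is not shown, and no other section explains how 42 was reached. Section 3 also says that the primary analyses follow intention to treat. According to sections 2.2 and 2.3, the blood outcomes are taken only at baseline and week 12.

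**The concern.** An attrition rate is a share of those who enter the trial. The allowance therefore has to be checked by applying 30% to the 42 randomised and comparing the remainder with 32. On that check the plan misses its own requirement. The likely cause is a familiar slip: adding 30% of the required number instead of dividing by the proportion expected to stay.

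What is at stake is whether the headline sample size, the attrition rate and the power statement can all be true together. As printed they cannot. Anyone relying on the sentence would believe that the trial can lose 30% of its participants and still have the 32 it says it needs.

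**Working it through.** **Inputs, all from section 3:** 32 required in total (16 per arm at 1:1), 80% power, two-sided 0.05, attrition 30%, target 42 (21 per arm).

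**Step 1. Reproduce the printed 42.**
- Required number × (1 + attrition): 32 × 1.30 = 41.6, rounded up to 42. Per arm: 16 × 1.30 = 20.8, rounded up to 21. Both match the article.
- Required number ÷ (1 − attrition): 32/0.70 = 45.7, rounded up to 46. Per arm: 16/0.70 = 22.9, rounded up to 23. Neither matches.

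The printed figure is thus consistent with multiplying by 1.3. This is inferred from the match, because the formula is not shown.

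**Step 2. Apply the stated attrition to the stated target.**
- 42 × 0.70 = 29.4 expected completers (21 × 0.70 = 14.7 per arm).
- Shortfall against 32: 32 − 29.4 = 2.6, or 3 if 29 whole participants are counted.

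This result does not depend on how 42 was reached.

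**Step 3. Find the attrition that 42 can absorb.**
- (42 − 32)/42 = 10/42 = 23.8%.

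**Step 4. Find the number that fits 30%.**
- 46 × 0.70 = 32.2, which meets 32. 45 × 0.70 = 31.5, which does not.
- If each participant independently has a 30% chance of leaving, the binomial probability of at least 32 completers is about 24% with 42 randomised and about 60% with 46.

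**Step 5. Translate into power, conditionally.** Suppose that 32 (16 + 16) does give 80% power in a two-group t-test. By the noncentral t distribution, this implies a standardised difference of about 1.02. At that difference:

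| Completers | Power |
|---|---|
| 16 + 16 | 80.0% |
| 15 + 14 | 75.7% |

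**Step 6. Check the condition in step 5.** The standardised difference of 1.02 is not in the article. If 1.7 ± 0.5 is read as a mean difference and its SD, the standardised difference is 1.7/0.5 = 3.4. Three per arm then already give about 87% power, and 16 per arm give almost 100%. So 32 does not follow from the printed effect on that reading. The article does not say whether 0.5 is an SD or a standard error, or whether the change is within or between groups.

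**The case against.** **Intention to treat might seem to close the gap.** It does not. Participants can be analysed as randomised only where an outcome exists or is filled in. A woman who leaves before week 12 has no post-baseline HOMA-IR, and the article describes no way of recovering it. The article adds an attrition allowance to the required 32, so it treats dropouts as lost to the analysis.

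**The effect is small.** This stands. The gap is about 3 completers, or 4 more randomised. It biases nothing and leaves the analysis unchanged. The Discussion presents the trial as small and its results as preliminary, although the Introduction makes efficacy the primary aim.

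**A reader might infer that the trial will fall below 80% power.** The article does not support that as a flat statement. The 76% in step 5 assumes that 32 is the correct number for 80%. With 1.7 ± 0.5 read as mean and SD, 29 completers would have almost 100% power. The supportable claim is narrower: expected completers fall below the plan's own 32.

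**A reader might also infer from the Discussion that 30% is itself too low,** since it reports that "up to 47% of women were lost to attrition". That is an upper figure from other trials, which studied weight loss. It is cited in support of a diet that does not require weight loss, and it is not this trial's planning assumption. How realistic 30% is remains a planning judgement separate from this arithmetic.

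**Conclusion.** The sample-size sentence is wrong as written. At the stated 30% attrition, 42 randomised leave about 29 completers against a stated need of 32, and 42 retains 32 only up to about 24% attrition. This rests on the article's own three figures (32, 30% and 42) and on reading attrition in the usual way, as a proportion of those randomised. It needs no effect size.

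That the error came from multiplying by 1.3 is very likely but not documented. The loss of about 4 percentage points of power (80% to about 76%) is conditional on an unverified 32 and should be quoted only with that condition. The point should be fixed. It does not threaten the validity of the trial.

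**What to change.** Correct the sentence in section 3 in one of two ways that need no effect size and no extra participants:

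- state that 42 randomised (21 per arm) retains 32 completers only if attrition is at most about 24%; or
- keep 30% and state that about 29 completers are then expected, fewer than the 32 on which the 80% power rests.

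Either costs one sentence. For information, holding 32 completers at 30% attrition corresponds to 46 randomised (23 per arm). That would mean 4 more participants and a matching change to the Abstract.

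If a power figure for 29 completers is printed, mark it as conditional on 32 being the correct number for 80%. Before relying on it, the sponsor should state what 1.7 ± 0.5 represents and how 32 was derived from it.

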## 4. Discussion

This study presents a novel intervention examining the efficacy of an ad libitum MedDiet intervention on cardiometabolic, hormonal and anthropometric features in overweight and obese women with PCOS. To the best of our knowledge, this will be the first study of its kind to examine the potential benefits of a MedDiet intervention in women with PCOS, without the need for caloric restriction. Typically, dietary interventions targeted for overweight and obese women with PCOS are designed to create a caloric deficit to elicit weight loss. However, achieving caloric restriction and weight loss targets has previously been shown to be challenging compared to women without PCOS [16].

In a secondary analysis of four clinical trials assessing the effect of weight loss on anthropometric, reproductive, metabolic and/or psychological outcomes in women with PCOS (*n* = 221), Moran et al. [73] reported that although 63% of women achieved clinically significant weight loss of ≥5% over a 2–8 month intervention period, up to 47% of women were lost to attrition, which is also consistent with previous literature [74,75,76]. Given that IR is a prominent clinical feature in the pathophysiology of PCOS, a dietary approach based on key principles of a MedDiet, without the need for weight loss, may indeed represent a novel dietary intervention for women with and without obesity. In a case–control observational study of Italian women (*n* = 112 with PCOS; *n* = 112 controls), greater adherence to a MedDiet was inversely associated with IR and hyperandrogenemia [77]. Moreover, the investigators further reported marked differences in the habitual dietary behaviours between the two groups, whereby women with PCOS consumed less EVOO, legumes, fish/seafood, and nuts compared to women without PCOS. In corroboration with the aforementioned study, Cutillas-Tolín et al. [78] reported that adherence to a MedDiet was protective against clinical phenotypic features of PCOS, namely hyperandrogenism and oligo-anovulation. Moreover. Barrea et al. [79] recently reported that poor adherence to a MedDiet was associated with a ‘metabolically unhealthy obesity’ phenotype in women with PCOS, as defined through evaluation of endocrine-metabolic profiles, inflammatory status, cardiometabolic indices and body composition parameters. Nevertheless, the absence of well-designed clinical trials exploring the efficacy of a MedDiet intervention in women with PCOS represents a notable gap in the research literature.

An important strength of our study is to explore the acceptability and feasibility of a MedDiet intervention in a non-Mediterranean population. Although the MedDiet is one of the most widely reported dietary patterns, much of the evidence from robust clinical trials has previously been conducted in Mediterranean populations [80,81], with few Australian clinical trials reporting on the efficacy and acceptability of a MedDiet intervention [82]. Nevertheless, despite its traditional origins, the translation of a MedDiet to non-Mediterranean populations is indeed appealing. Two previous feasibility studies delivering a MedDiet intervention reported that participants felt confident in their capabilities of long-term adherence to the dietary pattern [50,83]. However, our previous work [64] showed that while the majority (75%, *n* = 606) of Australian consumers perceived health benefits associated with adherence to the MedDiet, they also identified a number of barriers that would limit their ability to adhere to the diet, including knowledge, motivation, affordability, time and suitability. To the best of our knowledge, this will be the first study to explore the acceptability and feasibility of a MedDiet intervention in women with PCOS. Importantly, these data will provide a better understanding of the unique barriers and enablers to dietary change from the perspectives of women with PCOS. As such, use of COM-B model will aid in a deeper understanding as to why women with PCOS adhere and/or are unable to adhere when following a MedDiet intervention, allowing tailoring of future interventions around these barriers and enablers to enhance uptake of future interventions.

Another important strength of this study is that the delivery of the MedDiet intervention is based on an evidenced based theoretical framework. There is evidence to suggest that lifestyle change interventions that are informed by evidence-based behaviour change principles are more effective than those without [84,85]. Importantly, the COM-B model provides a systematic and transparent framework of identifying target behaviours and behaviour change techniques that are deemed to be most effective in behaviour change [69]. Specifically, patient-centered goal setting and improving self-efficacy through the provision of personalized one-on-one counselling and professional support has previously been identified a major facilitator to lifestyle reform amongst women with PCOS [67,86,87,88]. Nevertheless, there is a paucity of studies in PCOS that have applied theoretical frameworks and/or clearly defined and described behavioural change components, making the generalizability and transferability of study findings challenging. Importantly, in the proposed study, the information gained from the structured interviews with PCOS participants will further provide insights that are indeed unique to women with PCOS, including the BCTs used as part of the BCT taxonomy. Lastly, ongoing consultation with potential key stakeholders, including end users and healthcare providers, is an important strength of this study. As such, understanding the experiences and needs of women with PCOS and their healthcare providers in the delivery of evidence-based guidelines is an important step in the development of a theory-based PCOS lifestyle program and successful implementation of behaviour change strategies in order to achieve real-world impact [89].

Whilst the proposed study has several strengths, it also important to acknowledge its limitations. Specifically, we had a lack of available funds to collect additional cardiometabolic parameters including lipids and markers of systemic inflammation. Moreover, we have not included an assessment of psychological distress, in particular mood, depression and anxiety, all of which are particularly pertinent in women with PCOS. Given that this is intended to be a small study with very specific study aims and objectives, prioritization of data collection has been limited to cardiometabolic, hormonal and anthropometric features of PCOS. Importantly, our results will provide preliminary evidence which can be further explored using longer-term and adequately powered multimodal clinical trials investigating the feasibility of a MedDiet intervention, coupled with additional lifestyle related behaviour changes such as physical activity and mindfulness, on changes in body composition, cardiometabolic parameters, inflammation, menstrual cyclicity, fertility, depressive symptomology, and quality of life in overweight and obese women with PCOS.

Importantly, results from this study will offer an evidence-based dietary approach for the management of PCOS. As a secondary outcome of the study, we will also identify the acceptability and feasibility of a MedDiet in women with PCOS. Being able to identify and address potential barriers as well as gain useful insight into specific BCTs is an important step for informing effective and acceptable dietary interventions specific to the management of PCOS that are useful and effective in clinical practice, which is indeed an important strength of the proposed study. Future publications will detail major outcomes from this proposed study. Moreover, we will also communicate our findings more broadly to nutrition professionals and other health-care professionals including General Practitioners, Endocrinologists and Obstetricians, Gynecologists and Allied Health professionals. Specifically, we expect that our findings will also contribute to the future development of consumer and health professional resources and health professional training around the principles of a MedDiet. Lastly, we also expect that our findings could contribute to the evidence base for future iterations of the lifestyle management section of the international evidence-based guidelines for the assessment and management of PCOS [22], with a particular focus on specific therapeutic dietary interventions.

